### Randomization and allocation concealment

2.6

A statistician, a member of the Sichuan Traditional Chinese Medicine evidence-based Medicine Center, will generate 124 random serial numbers using the SAS 9.2 software (SAS, Cary, NC). Randomization will be accomplished after screening and baseline assessment, and eligible participants with DKD will be allocated to either the experimental group or the control group in a 1:1 ratio. The group numbers will be sequential and will be placed in sealed envelopes composed of carbon-free paper. The envelopes will be maintained by a study administrator who will not directly participate in the recruitment or follow-up of any participant, and the group numbers will be subsequently disclosed. On the day of inclusion, the administrator will open the envelope and provide the participant with their group number. Thus, all relevant individuals will remain unaware of group allocation until the study completion.

### Double-blind treatment

2.7

This study is a double-blind design, in which neither the researchers nor the participants will be aware of the treatment group during the trial period. Both LDP granules and placebo granules will be produced, packaged, and marked by Sichuan Green Pharmaceutical Technology Development Co Ltd to ensure that the granules are identical in relevant physical characteristics, such as appearance, shape, smell, and specifications. Additionally, the research team members will not communicate with the subjects regarding treatment group allocation. In the case of emergencies only, such as serious adverse events, or if the patient requires emergency treatment, the researchers will report to the principal researcher to determine whether the treatment should be disclosed.

### Diagnostic criteria

2.8

Participants must meet the western medicine diagnostic criteria for DKD (Table 1) as stated in the 2014 “Consensus of Experts on Prevention and Treatment of DKD” of the Chinese Diabetes Society,^[35]^ as well as the TCM syndrome diagnostic criteria of a syndrome of deficiency of kidney yin (Table 2). Syndrome differentiation will be independently determined by 2 designated associate chief or chief physicians, ranked above TCM physicians.^[36]^

**Table 1 T1:**
[figure not shown]
Western medicine diagnostic criteria for DKD.

**Table 2 T2:**
[figure not shown]
Diagnostic criteria for traditional Chinese medicine differentiation of syndrome of deficiency of kidney yin.

### Eligibility criteria

2.9

Inclusion criteria:

1.Patients were diagnosed with DKD meeting the criteria of the 2014 “Consensus of Experts on Prevention and Treatment of DKD” of the Chinese Diabetes Society;2.Patients aged between 25 and 75 years;3.Estimated GFR (eGFR) ≥ 30 mL/min/1.73 m^2^ without dialytic treatments;4.For patients with hypertension, blood pressure ≤140/90 mm Hg; for elderly, systolic blood pressure ≤150 mm Hg;5.Glycosylated hemoglobin (HbA1c) ≤7%; for patients with serious complications such as recurrent hypoglycemia, severe microvascular or macrovascular complications, or if it is difficult to meet the standard requirements despite adequate treatment, then HbA1c ≤8%;6.Patients with the ability to read, understand, and write research-related materials, and voluntarily comply with all test requirements;7.Patients voluntarily participating in the study and provide written informed consent.

Exclusion criteria:

1.Severe infection, anemia, electrolyte imbalance, or acute complications of diabetes mellitus in the previous 4 weeks;2.Severe cardiac, cerebral, hepatic, or hemorrhagic diseases, including cerebral infarction, cerebral hemorrhage, transient ischemic attack, myocardial infarction, unstable angina, heart failure, and hepatic inadequacy with aspartate transaminase or alanine aminotransferase levels more than twice the normal upper limit;3.Use of corticosteroids or immunosuppressants in the previous 3 months;4.Oliguria, anuria, severe edema, massive pleural, or peritoneal effusion;5.Renal transplantation;6.Mental disorders;7.Pregnancy or lactation;8.Allergy to trial drugs;9.Participation in other clinical studies;10.Incomplete understanding of the study, refusal to participate, or missing signed informed consent.

### Termination and withdrawal criteria

2.10

All participants will be informed that they have the right to withdraw from the trial and that they will receive the standardized treatment if they chose to withdraw. The reason for withdrawal will be recorded precisely in the case report form (CRF). The criteria for discontinuing treatment and withdrawing patients from the research project are as follows:

1.Manifestation of diseases or conditions mentioned in the exclusion criteria during the study period;2.Severe complications and/or general health deterioration;3.Detection of serious adverse events;4.Rapidly increasing serum creatinine (SCr) levels (>50% of baseline) or end-stage renal disease;5.Violation of study protocol;6.Voluntary withdrawal from the trial or loss to follow-up.

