### Outcome measures

3.2

Primary outcome: The primary outcome is determined as the change in 24h UP, from the baseline to the end of the treatment phase (week 24).

Secondary outcomes:

1.Changes in SCr and eGFR: eGFR will be used to assess the kidney function of participants with CKD-EPI creatinine equation of 2009^[37]^ (at weeks 4, 8, 12, 16, 20, 24).2.Change in the urinary albumin excretion rate from baseline to week 24 (at weeks 4, 8, 12, 16, 20, 24).3.Improvement of TCM syndromes and symptoms from baseline to week 24 (at weeks 4, 8, 12, 16, 20, 24).4.Changes in FBG and postprandial 2-hour blood glucose (2h PG) from baseline to week 24 (at weeks 4, 8, 12, 16, 20, 24).5.Changes in blood lipids from baseline to week 12 and week 24, including total cholesterol, triglyceride, HDL cholesterol, and LDL cholesterol (at weeks 4, 8, 12, 16, 20, 24).

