### Compliance

3.4

Once patients are randomized, researchers at the study sites will make all reasonable efforts to follow the patient for the duration of the study. During each visit, adherence to the intervention will be monitored and participants will be asked to return all study containers with any unused packs of granules, including all empty containers. All examination and transportation costs will be covered, and the results of physical examinations will be explained at every visit. Before every visit, messages will be sent via WeChat or by phone to remind patients regarding the imminent data collection. Additionally, ongoing support, such as free registration and treatment advice, will be provided to the participants during the follow-up phase.

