### Statistical analysis

3.7

All data analyses will be conducted according to the intention-to-treat principle. Missing values will be replaced by the last observation carried forward method. Two similar participants with complete data will be double-checked to ensure that the data are correct before analysis.

The data will be analyzed using the Statistical Package for the Social Sciences version 22.0 (SPSS 22.0, Chicago, IL). The analytical methods will be selected according to the distribution characteristics of the data. The measurement data will be examined using group *t* tests or nonparametric tests, the count data will be tested using the Chi-square test or Fisher exact probability method, and the grade data will be evaluated using nonparametric tests. Compared with the baseline values, the measurement data will be assessed using paired *t* tests or nonparametric tests, and the count data will be examined using a nonparametric test. All statistical tests will be bilateral tests, and *P* values <.05 will indicate statistical significance.

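### One list both stops study treatment and withdraws patients from the study, so week-24 outcomes are not collected in patients who worsen or deviate and LOCF fills the gap

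*Protocol article*

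**What the plan says.** Section 2.10 introduces its list with "The criteria for discontinuing treatment and withdrawing patients from the research project are as follows". Among the six items are "Rapidly increasing serum creatinine (SCr) levels (>50% of baseline) or end-stage renal disease", "Detection of serious adverse events" and "Violation of study protocol", the last with no grade of severity. The list also covers severe complications or general deterioration, and any exclusion condition that appears during the study. Voluntary withdrawal and loss to follow-up share the final item.

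Four other sections bear on the point:

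- Section 3.2 makes change in 24h UP from baseline to week 24 the primary outcome. The first secondary outcome is "Changes in SCr and eGFR: eGFR will be used to assess the kidney function of participants", assessed every 4 weeks to week 24.
- Section 3.4 says that after randomisation "researchers at the study sites will make all reasonable efforts to follow the patient for the duration of the study".
- Section 3.5 says that a serious adverse event leads to immediate stopping of the intervention. It does not say that the patient leaves the study.
- Section 3.7 says "All data analyses will be conducted according to the intention-to-treat principle" and "Missing values will be replaced by the last observation carried forward method".

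The article nowhere provides for visits or a week-24 urine collection after a withdrawal under 2.10.

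**The concern.** Stopping a study drug and leaving a study are different events. An intention-to-treat comparison needs the outcome of every randomised patient, including those who stopped the drug. Section 2.10 merges the two events, and several of its triggers are related to outcome. A rise in SCr of more than 50% is itself a bad value of a secondary outcome, and kidney damage is one of the stated safety concerns in 3.3.

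The protocol-violation item may also reach the primary outcome. Section 3.1 bars other drugs that could affect urinary protein or renal function. A patient given such a drug because of worsening would breach the protocol and could be withdrawn.

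At stake are the week-24 values of patients whose course was unfavourable. If such withdrawals differ between arms in number or in kind, the randomised comparison is biased. No analysis plan can recover measurements that were not taken.

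**Working it through.** **1. The passages side by side.**

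| Event | Section 2.10 | Elsewhere in the article |
|---|---|---|
| Serious adverse event | Treatment stops and patient leaves the study | 3.5: the intervention stops; leaving the study is not mentioned |
| SCr rise above 50% or end-stage renal disease | Same | 3.2: SCr and eGFR are outcomes to week 24 |
| Protocol violation | Same | 3.7: intention-to-treat; 3.4: reasonable efforts to follow to the end |

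The row for serious adverse events is the clearest mismatch. The other two rows show tension.

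**2. What LOCF puts in place of the missing value.** A triggering SCr recorded at a visit would be carried forward, so the renal event itself stays visible. The week-24 24h UP would be replaced by the last available urine value. Section 3.2 names only baseline and week 24 for 24h UP, and the visit schedule in Figure 1 is not shown. If there is no interim 24h urine, the value carried forward is the baseline one and the recorded change is zero.

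**3. Planning figures (section 2.5).** Means are 100.6 and 89 mg/24 h, SDs 23 and 12, with 62 per group and 10% dropout.

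- Planned difference: 100.6 − 89 = 11.6 mg/24 h.
- Expected dropouts: 0.10 × 124 = 12.4 patients. The article gives no breakdown by cause.
- The printed sample-size expression, (1.96 + 1.28)² × (23² + 12²) / 11.6², evaluates to 52.5, so 53 per group and not the stated 56. That is a separate matter and this point does not depend on it.

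**4. Illustration of bias (assumed inputs).** Shift = extra proportion withdrawn in one arm × mean amount by which the true week-24 value exceeds the value carried forward. Assume an extra proportion of 0.05, about 0.05 × 62 = 3.1 patients in that arm.

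- Excess of one control SD: 0.05 × 23 = 1.15 mg/24 h; 1.15 / 11.6 = 10%.
- Excess of 100 mg/24 h: 0.05 × 100 = 5.0 mg/24 h; 5.0 / 11.6 = 43%.

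The upper input is extreme on the planning figures: 100 / 23 = 4.3 control SDs. The direction depends on which arm loses more patients. Extra losses on LDP would flatter LDP; extra losses on placebo would hide a benefit.

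**5. Illustration of dilution (equal withdrawal in both arms, assumed rates).** Power = Φ(difference / √((23² + 12²)/n) − 1.96). With all 62 per group measured, the standard error is √(673/62) = 3.295. Then 11.6 / 3.295 − 1.96 = 1.56, a power of 94.1%.

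| Withdrawn | Simply lost | LOCF, no effect yet accrued | LOCF, half the effect accrued |
|---|---|---|---|
| 10% | 91.6% | 88.7% | 91.7% |
| 20% | 88.3% | 80.4% | 88.7% |
| 30% | 83.8% | 69.3% | 84.9% |

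For the LOCF columns the difference is 11.6 × (1 − w) or 11.6 × (1 − w/2), where w is the proportion withdrawn and n stays at 62. For example, at 10% with no effect accrued, 10.44 / 3.295 − 1.96 = 1.21, which gives 88.7%. These figures show loss of power only, not bias.

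**The case against.** The strongest reply is that 2.10 removes nobody from an analysis. Intention-to-treat in 3.7 concerns the analyses, LOCF keeps withdrawn patients in them, adverse events are recorded whatever their cause, and the reason for withdrawal is recorded. A reader might infer from 2.10 that the plan deletes the outcomes it sets out to measure, or that it flatly contradicts intention-to-treat. The documents support neither reading. What is lost is observation after withdrawal, which creates missing data inside an intention-to-treat analysis.

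A reader might also take 3.4 as a guarantee of complete follow-up. It promises reasonable efforts only, in a section on adherence and retention, so it is in tension with 2.10 and does not contradict it outright.

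It can further be said that the article condenses a fuller protocol (2.3 mentions version 2.0), which may provide for visits after treatment stops, and that 3.5 suggests the wording of 2.10 is loose and not deliberate. Both are possible. But the printed sentence states a rule and does not merely leave a detail out, and sites that follow it would stop collecting data.

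Finally, the inputs for the size of the bias are assumed. That stands in full.

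**Conclusion.** The point holds as a flaw that should be fixed. Section 2.10 as printed ends data collection for outcome-related reasons and for any protocol violation, and LOCF then fills in week-24 24h UP, SCr and eGFR with earlier values. It does not match 3.5, it is in tension with 3.4, and it undermines the aim stated in 3.7.

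The size of the bias cannot be derived from the documents, which give no withdrawal rate by criterion or by arm. The range of 1.15 to 5 mg/24 h (10% to 43% of 11.6) rests on two assumptions: 5 extra withdrawals per 100 in one arm, and a true excess of 23 to 100 mg/24 h. Only the lower excess is tied to a planning SD.

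A reader might infer that the 12 or so expected dropouts will be mainly the patients with the worst outcomes. The triggers make some such clustering plausible, but the article does not say so, and ordinary loss to follow-up is part of the same list.

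**What to change.** Reconcile 2.10 with 3.4, 3.5 and 3.7 by splitting it in two:

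- **End of study granules.** Leave the clinical criteria as they are; no view is taken here on which are right.
- **End of data collection.** Limit this to withdrawn consent for further data, or loss to follow-up.

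Add that patients who stop granules for any other reason, protocol violation included, are asked to attend the remaining scheduled visits, to give the week-24 24h urine and SCr where feasible, and are analysed as randomised.

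The cost is a short amendment, which under 2.3 needs Ethics Committee approval. The visits are already scheduled, and 3.4 says examination and transport costs are covered. The amendment should come before withdrawals accrue, because missed measurements cannot be recovered later.

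The downside is that off-treatment week-24 values enter the primary analysis and may dilute the effect somewhat. If stopping left no effect at week 24, the dilution would be like the no-effect column above (88.7% power at 10%). Unlike carried-forward values, however, these would be the patients' actual outcomes.

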### Study drugs

2.11

Study drugs to be evaluated include LDP and LDP simulation agents (placebo), which will be manufactured by the Sichuan Green Pharmaceutical Technology Development Co Ltd (Sichuan, China). The ingredients present in LDP are as follows: Radix Rehmanniae (Shu dihuang) at a dose of 24 g, *C officinalis* (Shan zhuyu) at a dose of 12 g, Chinese yam (Shan yao) at a dose of 12 g, Poria cocos (Fu ling) at a dose of 9 g, Alisma (Ze xie) at a dose of 9 g, and Cortex Moutan Radicis (Mu danpi) at a dose of 9 g. All ingredients present in the prescription will be processed to form granules by pharmaceutical manufacturers. The granules will be packaged into paper packets at a dose of 10 g. The placebos will be composed of starch, without the active ingredients. By adding various materials, the placebos will be produced such that they are identical in appearance and taste to the LDP granules.

## Interventions

3

### Treatment plan

3.1

Both groups will be treated using western medicine in accordance with the 2014 “Consensus of Experts on Prevention and Treatment of DKD” of the Chinese Diabetes Society.^[35]^ This includes blood glucose control (metformin hydrochloride sustained-release tablets; Trade name: Meperidine, Specification: 0.5 g × 30 seconds, Manufacturer: SPH Sine Pharmaceutical Laboratories Co, Ltd, Batch number: H20050699; Oral, 0.5 g per time, once a day) and blood pressure control (Irbesartan tablets; Trade name: APROVEL, Specification: 150 mg × 7 tablets, Manufacturer: Hangzhou Sanofi Pharmaceutical Co, Ltd, Batch number: J20080061; Oral, 150 mg once a day). Simultaneously, participants will be informed regarding diabetes health, diet control, including limited protein intake, and the need for regular exercise.

Experimental group: Patients in the experimental group will receive LDP granules at a dose of 10 g twice daily for 24 weeks, after breakfast and dinner, dissolving 10 g granules into 100 mL warm boiled water.

Control group: Participants in the control group will receive placebo granules at a dose of 10 g twice daily for 24 weeks. The measurements will be the same as in the experimental group.

During the trial period, no other drugs that could affect urinary protein or renal function will be permitted.

### Outcome measures

3.2

Primary outcome: The primary outcome is determined as the change in 24h UP, from the baseline to the end of the treatment phase (week 24).

Secondary outcomes:

1.Changes in SCr and eGFR: eGFR will be used to assess the kidney function of participants with CKD-EPI creatinine equation of 2009^[37]^ (at weeks 4, 8, 12, 16, 20, 24).2.Change in the urinary albumin excretion rate from baseline to week 24 (at weeks 4, 8, 12, 16, 20, 24).3.Improvement of TCM syndromes and symptoms from baseline to week 24 (at weeks 4, 8, 12, 16, 20, 24).4.Changes in FBG and postprandial 2-hour blood glucose (2h PG) from baseline to week 24 (at weeks 4, 8, 12, 16, 20, 24).5.Changes in blood lipids from baseline to week 12 and week 24, including total cholesterol, triglyceride, HDL cholesterol, and LDL cholesterol (at weeks 4, 8, 12, 16, 20, 24).

### Safety assessment

3.3

In China, LDP granules have been used for over 1000 years, and the dosage to be used in this study is within the recommended range based on the People's Republic of China Pharmacopeia (2015 edition). Moreover, we will employ a series of measures, including subjective descriptions and laboratory tests, especially focusing on heart, liver, and kidney damage, to assess the safety of LDP granules, from the time of enrollment through the follow-up period.

### Compliance

3.4

Once patients are randomized, researchers at the study sites will make all reasonable efforts to follow the patient for the duration of the study. During each visit, adherence to the intervention will be monitored and participants will be asked to return all study containers with any unused packs of granules, including all empty containers. All examination and transportation costs will be covered, and the results of physical examinations will be explained at every visit. Before every visit, messages will be sent via WeChat or by phone to remind patients regarding the imminent data collection. Additionally, ongoing support, such as free registration and treatment advice, will be provided to the participants during the follow-up phase.

### Adverse events

3.5

Any adverse events will be recorded in CRFs, irrespective of their relationship to the study intervention. In the case of any serious adverse events, the intervention will be immediately discontinued and a detailed description of the time, severity, relationship with the drug, and the measures taken based on standard operating procedures of the China Food and Drug Administration will be recorded. Additionally, serious adverse events will be reported to the Steering Committee and Ethics Committee within 24 hours.

### Data management and quality control

3.6

All records will be collected in CRFs, which will be completed by a trained and qualified investigator. Once a CRF is completed, the original record will not be altered if any corrections are to be made. The completed CRFs will be reviewed by a clinical inspector.

Data entry and management will be guided by medical statisticians. To ensure data accuracy, 2 data administrators will input and proofread the data independently. After reviewing and confirming that the established database is accurate, the data will be locked by the main researchers and statistical analysts. Thereafter, the locked data or files will not be altered and will be submitted for statistical analysis by the research group. The Sichuan TCM evidence-based Medicine Center (Chengdu, China), which has no competing interests in terms of this study, will be responsible for monitoring the data. Furthermore, data audits will be performed during the trial by the Department of Science Research, at the hospital of the Chengdu University of TCM, independent of the investigators.

### Statistical analysis

3.7

All data analyses will be conducted according to the intention-to-treat principle. Missing values will be replaced by the last observation carried forward method. Two similar participants with complete data will be double-checked to ensure that the data are correct before analysis.

The data will be analyzed using the Statistical Package for the Social Sciences version 22.0 (SPSS 22.0, Chicago, IL). The analytical methods will be selected according to the distribution characteristics of the data. The measurement data will be examined using group *t* tests or nonparametric tests, the count data will be tested using the Chi-square test or Fisher exact probability method, and the grade data will be evaluated using nonparametric tests. Compared with the baseline values, the measurement data will be assessed using paired *t* tests or nonparametric tests, and the count data will be examined using a nonparametric test. All statistical tests will be bilateral tests, and *P* values <.05 will indicate statistical significance.

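### Last observation carried forward is the only missing-data method, although patients are withdrawn for deterioration; this may bias the week-24 24h UP comparison in either direction

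*Protocol article*

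**What the plan says.** All of this is in the protocol article.

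- **Section 3.7, Statistical analysis.** The analysis set: "All data analyses will be conducted according to the intention-to-treat principle". Missing data: "Missing values will be replaced by the last observation carried forward method". No other method and no sensitivity analysis is named. Between-arm comparisons are t tests or nonparametric tests; comparisons with baseline within each arm are paired t tests or nonparametric tests.
- **Section 2.10, Termination and withdrawal criteria.** The list opens: "The criteria for discontinuing treatment and withdrawing patients from the research project are as follows". It includes "Severe complications and/or general health deterioration", "Detection of serious adverse events" and "Rapidly increasing serum creatinine (SCr) levels (>50% of baseline) or end-stage renal disease". It also includes protocol violation, voluntary withdrawal and loss to follow-up.
- **Section 3.2, Outcome measures.** The primary outcome is the change in 24h UP from baseline to week 24, with no intermediate visit listed. Every secondary outcome, including SCr, eGFR and urinary albumin excretion rate (UAER), is listed at weeks 4, 8, 12, 16, 20 and 24.
- **Section 3.4, Compliance.** After randomization, "researchers at the study sites will make all reasonable efforts to follow the patient for the duration of the study". Nothing says whether this covers patients withdrawn under Section 2.10.
- **Section 2.5, Sample size.** Planned difference 100.6 − 89 = 11.6 mg/24 h, SDs 23 and 12, dropout 10%, 62 per group.

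**The concern.** LOCF is adequate only if a patient's value would have stayed where it was last seen. Section 2.10 makes that doubtful, because several of its triggers are forms of worsening and the patient leaves the project, not only the study drug. A value from before or at the start of the worsening then stands in for week 24.

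Three things are at stake. The first is the primary between-arm difference: if more patients on one arm leave because they worsen, or worsen more afterwards, that arm is flattered. The second is the within-arm paired tests, where nothing cancels. The third is the standard error, because imputed values enter the t test as if measured. The intention-to-treat label does not help, since the week-24 outcome of these patients is assumed rather than observed.

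The method is stated outright, so this is not a detail left to an analysis plan.

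**Working it through.** **Inputs from Section 2.5.** Difference 11.6 mg/24 h; SDs 23 and 12, so pooled SD = √((529 + 144)/2) = 18.34; 62 per arm; dropout 10%, about 6 of 62 per arm.

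**The plan's own figure.** (1.96 + 1.28)² × (23² + 12²)/11.6² = 10.50 × 673/134.56 = 52.5, so 53 per group where the article gives 56. From 56, the dropout step gives 61.6 (× 1.1) or 62.2 (÷ 0.9), consistent with 62. The mismatch at 56 is a separate matter and has no bearing here. With 62 fully observed per arm, t-test power for 11.6 is about 94%.

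**Inputs that are assumptions.** The documents give neither the share withdrawn for worsening in each arm (w) nor the rise in 24h UP after the carried value (X). I take 15% versus 5%, which averages to the planned 10%, and X = 11.6, 23 or 46 mg/24 h.

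**Step 1: bias.** If the values LOCF uses have mean m in an arm, the true week-24 mean is m + wX, so LOCF understates that arm by wX. For control minus LDP:

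bias = X × (w_LDP − w_control), where a positive value favours LDP.

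| X (mg/24 h) | Bias, 15% LDP vs 5% control | Share of 11.6 | Type I error if no true effect (SD 23 in both arms) | Power if 5% LDP vs 15% control (bias of opposite sign) |
|---|---|---|---|---|
| 11.6 | 0.10 × 11.6 = 1.16 | 10% | about 6% | about 88% |
| 23 | 0.10 × 23 = 2.3 | 20% | about 8% | about 80% |
| 46 | 0.10 × 46 = 4.6 | 40% | about 20% | about 55% |

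The last two columns come from simulation with 62 per arm and a Welch t test. With 10% in each arm and the same X, the between-arm bias is zero.

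**Step 2: within-arm tests.** Here the error is wX in each arm, with no cancellation. At w = 10% it is 0.10 × 11.6 = 1.2 to 0.10 × 46 = 4.6 mg/24 h, even when dropout is balanced.

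**Step 3: no intermediate 24h UP.** If only baseline precedes week 24, the carried value is baseline and the change is 0. With 10% dropout per arm, the expected difference is 0.9 × 11.6 = 10.44.

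For power, the zeros also reduce the spread. Take SD of change 18.34, mean change 0 on control and −11.6 on LDP:

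- control variance = 0.9 × 336.5 = 302.9
- LDP variance = 0.9 × 336.5 + 0.9 × 0.1 × 11.6² = 302.9 + 12.1 = 315.0
- pooled SD = √((302.9 + 315.0)/2) = 17.6
- standardized difference = 10.44/(17.6 × √(2/62)) = 3.30, so power ≈ Φ(3.30 − 1.96) ≈ 91%

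Simulation agrees at about 91%. With 56 completers per arm and no imputation, power is 91.3%.

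**The case against.** **Bias is not shown, only a risk of it.** Between arms it needs unequal withdrawal or unequal later worsening. The documents suggest neither, and Section 2.5 plans one dropout rate for both groups. Section 2.10 also covers violation, voluntary withdrawal and loss to follow-up, with no split. This stands, and it is why the point is worded as a possible bias of unknown sign.

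**Extreme scenarios prove little.** A reader might infer that LOCF could reverse the trial's conclusion. With 15% LDP versus 5% placebo withdrawn, a 100 mg/24 h rise in every withdrawn patient and baseline carried forward, simulation gives an LOCF effect of about −9.9 with P < .05 in 88% of trials, against −1.5 and 6% with everyone measured. But 100 mg is about 5.5 of the planned SDs (100/18.34), every withdrawal is taken to be outcome-driven, and the absence of interim 24h UP is unconfirmed. The documents do not support it as an expected size.

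**The power loss is small.** A reader might put power under baseline carried forward at 88.2%, but that keeps the SD at 18.34 while shrinking the difference. The correct figure is about 91%, close to that for completers alone. The dilution to 10.4 stands, and it works against LDP.

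**SCr and eGFR are less exposed to the renal trigger.** They are listed every four weeks, and a withdrawal triggered by SCr needs a measured rise, so LOCF would normally carry the raised value. This stands. Likewise, if 24h UP is taken at the triggering visit, the carried value may already show some worsening; and the link from SCr to 24h UP is plausible but assumed.

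**Section 3.4 promises follow-up.** It softens the point but does not settle it, since nothing secures a week-24 sample after a Section 2.10 withdrawal.

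**Conclusion.** The concern holds as a risk. The protocol fixes LOCF as its sole missing-data method while its withdrawal rules tie missing week-24 values to worsening. LOCF's assumption of no later change is then hard to defend, and it overstates precision.

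Under the assumed 15% versus 5% split and a rise of 11.6 to 46 mg/24 h, the primary difference moves by about 1.2 to 4.6 mg/24 h, towards or away from LDP. That is 10% to 40% of the planned effect. Balanced withdrawal with equal worsening gives no between-arm bias, but the paired tests are still affected. If 24h UP is measured only at baseline and week 24, 10% dropout per arm dilutes 11.6 to about 10.4, with power still about 91%.

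It would go too far to say that the primary result will be biased, or biased in LDP's favour: the documents give no withdrawal split by arm, no size of later worsening and no visible schedule for 24h UP.

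**What to change.** Replace the LOCF sentence in Section 3.7:

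1. **Primary outcome.** Multiple imputation by arm of week-24 24h UP, using baseline 24h UP and the scheduled UAER, SCr and eGFR values, followed by a baseline-adjusted comparison. If 24h UP is measured at each visit, use a mixed model for repeated measures instead.
2. **Serial secondary outcomes.** Mixed models for repeated measures.
3. **Sensitivity.** One delta-adjusted analysis that assigns worse week-24 values to patients withdrawn for deterioration or serious adverse events. Keep LOCF, if at all, only as a further sensitivity analysis.
4. **Data collection.** Reconcile Sections 2.10 and 3.4 by stating whether week-24 data are collected after withdrawal.

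The analysis changes use standard routines and data already scheduled, with no extra patients or visits. The cost is wording and a little more analysis work; settle it before the data are locked.
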